## **Section 5: Statistical analysis**

SPSS v. 20.0 will be used for statistical analysis of the data. The data will be entered into Excel tables by double entry and checking to establish the database. The data of MAS and

MTS scales will be described in terms of means  $\pm$  standard deviation. If the data of MAS , and MTS scale did not conform to the conditions of normal distribution and homogeneity of variance, the Mann-Whitney test will be used; if the data of MAS and MTS scale did conformed to the conditions of normal distribution and homogeneity of variance, then independent sample t-test will be used. Pearson correlation analysis will be used for the correlation analysis between the GMFCS grade, gender and age and muscle tone after treatment in the Experiment Group. Either one-way ANOVA or Chi-squared test will be used for inter-group data comparison. A p-value less than 0.05 will be considered statistically significant.

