## **2.6 Sample size**

The number of subjects needed in each study group to test the primary hypothesis was determined based on previous clinical trials assessing spasticity in cerebral palsy children. A prior study by Auvichayapat [54] testing the effects of anodal tDCS on upper limb spasticity using Modified Ashworth Scale (MAS) found that a sample size of 46 individuals divided into two groups (1 mA a-tDCS [ $n = 23$ ], Sham a-tDCS [ $n = 23$ ]) had an effect associated with a power of 0.90 with an alpha level of 0.05 [57]. If the combined tPCS and TENS therapy in this study had a similar effect on our primary outcome measure of MAS, the authors determined that 60 participants (30 per condition) would be sufficient to provide a power of 0.90 with an alpha of 0.05, to which we will add 10 participants to compensate for possible dropouts, totaling 70 participants.

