## 2.8 Assessment

Evaluations using Modified Ashworth Scale (MAS) and Modified Tardieu Scale (MTS) will be conducted on all participants by two qualified rehabilitation doctors who have been involved in clinical work of pediatric rehabilitation for more than five years. The evaluators are blinded to the allocation of the children to the two groups and did not participate in the treatment of the subjects. A baseline evaluation and a post-treatment evaluation will be held. Both baseline and post-treatment evaluation will be conducted in a designated evaluation room that is spacious, quiet and bright, as follows:

- Baseline evaluation: three days prior to intervention
- Post-treatment evaluation: three days following last session of treatment
- Each scale will be repeatedly measured 3 times each time. Each score was the average of the three measurements.

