### 2.8.1 Modified Ashworth Scale (MAS) [53]

The MAS was used to evaluate muscle spasticity in the lower limbs. MAS evaluation involves the rater manually moving a limb through the range of motion to passively stretch specific muscle groups and a six-point ordinal scale for grading the resistance encountered during such passive muscle stretching. MAS grades of spasticity are as follows: 0 = normal muscle tone; 1 = slight increase in muscle tone, manifested by catch and release or by minimal resistance at the end; 1+ = slight increase in muscle tone, manifested by a catch, followed by minimal resistance throughout; 2 = more marked increase in muscle tone, but limb easily flexed; 3 = considerable increase in muscle tone, passive movement difficult; and 4 = limb rigid in flexion or extension.

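### The group comparison is an unadjusted t-test or Mann-Whitney test picked by a check on the outcome data; one pre-specified baseline-adjusted analysis would be more precise and would fix the estimand

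*Protocol*

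**What the plan says.** Section 2.6 of the protocol identifies the primary endpoint in passing, as "our primary outcome measure of MAS". Section 2.8 has both scales assessed in all participants at two visits: "A baseline evaluation and a post-treatment evaluation will be held". It adds "Each score was the average of the three measurements". Section 2.8.1 describes the MAS as "a six-point ordinal scale for grading the resistance encountered".

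Section 5 holds all of the analysis text. The between-arm test for MAS and MTS depends on a check of normality and equal variance. If the check fails on normality or "homogeneity of variance, the Mann-Whitney test will be used"; if the data pass on normality and "homogeneity of variance, then independent sample t-test will be used". No covariate appears in this comparison, and the text does not say whether the value tested is the post-treatment score or the change from baseline. Two further sentences matter: "Either one-way ANOVA or Chi-squared test will be used for inter-group data comparison", with no variables named, and "A p-value less than 0.05 will be considered statistically significant", with no sidedness given.

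**The concern.** There are two weaknesses in the stated method.

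First, a baseline measurement of the same scale is often a good predictor of the later score, and here it is collected in every child at no extra cost. Entry spans MAS grades I to IV, GMFCS levels III to V and ages 2 to 12 years, so baseline spread may be wide. A comparison that leaves baseline out carries that spread in its standard error.

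Second, the test is settled only after the outcome data have been inspected. The t-test addresses a difference in means. Mann-Whitney addresses the probability that a child in one arm scores higher than a child in the other. MAS and MTS could therefore end up with different tests and different estimands, although Section 5 describes both by means and standard deviations. Sending unequal-variance data to Mann-Whitney does not cure the problem either: its null distribution assumes that the two distributions are identical, so unequal spread disturbs it too.

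At stake are the width of the interval for the treatment effect and the clarity of what the primary result estimates.

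**Working it through.** **Inputs from the protocol.** Planned size 30 per arm with power 0.90 and alpha 0.05 (Section 2.6); prior study with 23 per arm and power 0.90 at alpha 0.05 (Section 2.6). No effect size, SD or correlation is given.

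**Assumptions.** Two-sided test; r, the baseline to post-treatment correlation, taken as 0.3, 0.5 and 0.7; equal SD at both visits.

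**The plan's own figure.** The 60 cannot be derived directly, because no effect size or SD is stated. Working back from the prior study:

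- Normal formula: d = (1.960 + 1.282) × √(2/23) = 0.956. Noncentral t: d = 0.977.
- Power of the planned t-test at 30 per arm for d = 0.977: 0.961.

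So 30 per arm is enough for an effect of that size, as the protocol claims.

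**Precision against post-treatment values.** The effect with exactly 90% power in an unadjusted t-test at 30 per arm is d = 0.851 (noncentral t; 0.837 by the normal formula). ANCOVA multiplies the variance by 1 − r². The effect in residual SDs becomes 0.851/√(1 − r²), and power comes from the noncentral t with 57 degrees of freedom (one spent on baseline).

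| r | 1 − r² | variance removed | 60/(1 − r²) | effect in residual SDs | power, 30 per arm |
|---|---|---|---|---|---|
| 0.3 | 0.91 | 9% | 66 | 0.892 | 0.925 |
| 0.5 | 0.75 | 25% | 80 | 0.983 | 0.963 |
| 0.7 | 0.51 | 49% | 118 | 1.192 | 0.995 |

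**Precision against change scores.** A change score has variance factor 2(1 − r). The ratio of ANCOVA to change score is (1 − r²)/[2(1 − r)] = (1 + r)/2, which never exceeds 1. The gain is therefore (1 − r)/2 of the variance: 35%, 25% and 15% at r = 0.3, 0.5 and 0.7. For d = 0.851 the change-score t-test has power 0.782, 0.900 and 0.987. Below r = 0.5 it is worse than ignoring baseline.

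**At the effect implied by the prior study.** For d = 0.977, ANCOVA at r = 0.5 raises power from 0.961 to 0.990.

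**The assumption check.** Section 5 names no check, so Shapiro-Wilk in each arm plus Levene, all at 0.05, was assumed and simulated with 30 per arm and 4,000 runs per scenario.

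- Type I error of the two-stage rule: 0.053 with normal data, 0.054 with single MAS-like ordinal grades. The simulation standard error is √(0.05 × 0.95/4000) = 0.0034, so both are compatible with 0.05.
- t-test branch chosen: about 86% of null runs with normal data, 0.6% with ordinal grades.
- The two tests disagreed on significance in about 2% of null runs and 4% to 8% of runs with a true effect.

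The branch taken thus depends heavily on the shape of the data. The simulated grades were single readings; averages of three could fall between the two cases.

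**The case against.** The best defence is that the comparison is already valid and its rule is written in advance. Most of that stands, and it rules out several stronger readings.

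- **Underpowered trial.** A reader might infer this from the lost precision. The documents do not support it: at the effect implied by the cited study, the planned test has about 0.96 power.
- **Bias from chance imbalance.** Allocation is unstratified. With a 35/35 split and a GMFCS level held by an assumed 30%, 40% or 50% of children, the arms differ by 20 points or more with probability 0.117, 0.087 or 0.151. But the unadjusted estimate is unbiased over randomisation and its standard error already reflects such imbalance. The cost is precision.
- **Inflated type I error.** The simulation gives no sign of it.
- **Three competing tests.** With two groups, one-way ANOVA is the equal-variance t-test (F = t², same p-value). Paired with chi-squared, the sentence plausibly concerns participant characteristics. It is unclear wording, not a third route to a primary result.
- **Baseline wholly unused.** If changes are tested, baseline is used. Section 5 does not say, so the 49% at r = 0.7 applies only if post-treatment values are tested; otherwise the gain is 15%.

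It is also fair that covariate lists are often left to an analysis plan. Here, however, the protocol is not silent: it names the unadjusted tests and the rule for choosing between them.

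**Conclusion.** The point holds as a gain in efficiency and clarity that should be taken. Section 5 commits to an unadjusted, data-selected test while baseline MAS and MTS are available for every child. ANCOVA would remove 9% to 49% of the variance over r = 0.3 to 0.7 if post-treatment values are tested, and 35% down to 15% over the same range if changes are tested. At r = 0.3 the gain over post-treatment values is modest. These figures rest on assumed correlations, a two-sided test and equal SDs at the two visits; the protocol gives none of these. Fixing the estimand has value whatever r is. The validity of the randomised comparison and the adequacy of the sample size are not put in doubt by this point.

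**What to change.** In Section 5, replace the assumption-test switch with one primary analysis: ANCOVA of the post-treatment MAS score on group and baseline MAS, with heteroscedasticity-robust standard errors, reporting the adjusted difference with its 95% CI. Use the same model for MTS with its own baseline. Because the MAS is ordinal, add a rank-based or ordinal model with the same baseline covariate as a sensitivity analysis. GMFCS level and age are optional further covariates. Limit the ANOVA/chi-squared sentence to baseline characteristics.

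For the model to be fully specified, the paragraph should also say which MAS score enters it (muscle group, side or summary) and what number grade 1+ takes when readings are averaged.

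The cost is one paragraph. No new data, visits or children are needed. The change should be made before outcome data are seen by arm.
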